### Interventions and comparisons

Potentially eligible women > 34 weeks gestation will be identified during their attendance at the antenatal clinic, antenatal classes, or midwifery group practice, or while an in-patient on the antenatal ward. Posters advertising the trial will be placed around the hospital in these areas. An "expression of interest" form will be made available where mothers can obtain contact information from our research coordinator and advised further about what is involved if participating in the trial. All women approached for eligibility will have a structured explanation regarding participating in the trial and numbered as per consort statement [59]. Potential trial participants are informed that they have a 66% chance of being allocated to one of the hypnosis interventions and a 33% chance of proceeding with their childbirth preparation as per the usual practice of our institution. Eligible women who decline to enter the trial will be asked for consent to allow us to collect routine birth outcome data without any other intervention. Reasons for declining to participate will be recorded as: not interested, against my religion, too busy, don't believe in it, declined randomisation, other. Other reasons for leaving the study prior to randomisation will be noted. For safety considerations the consent process will include permission from participants to inform their GP and obstetrician, if further clinical assessment or treatment for postnatal depression is indicated. All eligible women approached who decide to continue their preparation for childbirth outside the trial will be asked permission for us to collect birth outcome data so that we can compare primary outcomes of non participants with those of women randomised to our "no intervention" control group.

Study participants will have baseline demographic data collected including parity, health insurance status, highest level of formal education, marital status and the use of any complementary therapies such as acupuncture or yoga. At this time participants will be asked to complete Spielberger Stait/Trait anxiety[60] and Edinburgh post-natal depression scales[61]. In addition they will be tested for hypnotisability using the Creative imagination Scale (CIS). We deliver the scale by asking participants to listen to a standardised audio CD of the CIS in the presence of a researcher. Participants then complete an answer sheet detailing their imaginative experience on a 5 point Likert scale [62].

### Randomisation

Biomedical statisticians at our institution's Dept. of Public Health have arranged for a computer generated random number sequence, of unspecified block size stratified for parity. This randomisation plan will produce study arms of approximately equal size with similar numbers of nulliparous and multiparous participants.

### Allocation concealment

We will be provided with the group allocation for each individual participant via telephone or a networked computer program. Allocation concealment is assured as the participant ID, parity and eligibility for trial entry is confirmed and recorded centrally prior to verifying a participant's group allocation. Participants assigned to hypnosis groups are to be given appointments by our research assistant to commence antenatal group hypnosis training as near as possible to 37 weeks gestation.

### Consort criteria

All eligible women will be given a trial identification number as per consort statement (See Figure 1 Trial Flow)

**Figure 1 F1:**
[figure not shown]
**Title. **HATCh Trial Flow

### Ethics approval

Local Regional Ethics Committee approval has been obtained prior to recruitment. Recruitment commenced in December 2005.

### Trial registration

This trial has been registered with the Australian Clinical Trials register (ACTRN012605000018617) December-05 and at clinicaltrials.gov (NCT00282204) January-06.

### Treatment schedules

A researcher is responsible for base line data management, collection and co-ordinating appointments with the hypno-therapist and nurse supervising Group 1 and 2 participants respectively, directing women to their allocated interventions. Following baseline demographic data collection which includes the administration of the Edinburgh Postnatal Depression Scale (EPDS)[61], Spielberger[60] and Creative Imagination Scale (CIS)[62], trial participants are informed of where and when to attend their allocated sessions. The two interventions are administered in groups of up to ten women at our institution's group physiotherapy room. Participants allocated to an intervention are requested to attend sessions which are scheduled as near as possible to 37 weeks gestation and are held at weekly intervals for three consecutive weeks. Those women having a planned induction of labour will be allocated their hypnosis sessions as near as possible to commence within three weeks of the induction date rather than the original expected date of confinement (EDC).

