Since April 2002, we have been developing an antenatal hypnosis training program for women in late pregnancy (after 35 weeks gestation) to be utilised for anxiolysis and as an analgesia adjunct during childbirth. Initially, we were seeing women on an individual basis. However increasing demand for hypnosis preparation for childbirth from mothers, midwives and obstetricians at our institution has led us to our current practice of training groups of 5–10 women/week in self hypnosis techniques developed along the lines described by Waxman, [45]. McCarthy [21,46] and Bjenke [24]. The hypnosis training program has continued to develop over the last three years utilising advice from senior clinical hypnotherapists in Australia and New Zealand with expertise and substantial experience of preparing over 1000 women in hypnosis preparation for childbirth. The intervention lasts approximately one hour and the hypnosis sessions are held for three consecutive weeks. Birth outcomes of 77 antenatal women taught hypnosis in preparation for childbirth between January 2003 and August 2004 were compared with parity matched controls delivering after 37 weeks gestation during 2003 at our institution. Primiparous women, receiving hypnosis preparation, used fewer epidurals than controls 18/50 (36%) vs 765/1436 (53%) (RR0.68, 95%CI 0.47,0.98) and less augmentation 9/50 (18%) vs 523/1436 (36%) (RR 0.48, 95%CI 0.27,0.90) [47]. These findings are consistent with those of our systematic review [22].

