#### Statistical tests

Descriptive statistics Mean/sd for parametric data, Median and inter-quartile range for non-parametric data. For Dichotomous outcomes: Chi squared/Relative Risks with 95% confidence intervals. Regression analysis will be utilised to examine the influence of potential confounders on our outcomes of interest. NNT for benefit and harm where appropriate will be calculated.

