#### Sub-group analyses

Subgroup analyses of primary outcomes will be performed for women regarding; induced vs spontaneous labour; attendance at all three sessions, whether each session cd was used at least once; size of group < 3 women, hypnotist, women's hypnotisability as measured by the CIS, women's beliefs; on whether they were in experimental group, women's beliefs of the efficacy of hypnosis prior to labour, Women's expectations of requiring an epidural, Women's expectations of having a normal spontaneous birth, Previous experience of non childbirth hypnosis or yoga. hypnotisability as measured by the Creative Imagination Scale. Some women will not attend the sessions to which they are allocated. We have tailored the hypnosis intervention so that most of the skills are learned in the first session and nearly all the skills are delivered by the second session. The third session is for re-enforcement and consolidation. Any women giving birth prior to completing all three sessions will be analysed both on an "intention-to-treat" basis and with total session exposure as a predictor.

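### Both hypnosis arms are taught in shared groups, but the named tests and the sample size treat all women as independent; if outcomes correlate within session groups, standard errors are likely too small

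*Protocol article*

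**What the plan says.** All references are to the protocol article.

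- **Unit of randomisation.** Allocation concealment describes allocation woman by woman; Randomisation adds stratification by parity.
- **Delivery.** Under Treatment schedules, "The two interventions are administered in groups of up to ten women", with sessions "held at weekly intervals for three consecutive weeks". The sections on Groups 1 and 2 describe what is shared: talk about fears and answers to questions in Group 1, and question time at each session in Group 2. The Group 3 section gives control women no trial sessions.
- **Group size.** Ten is a ceiling. The Background reports pre-trial practice as "training groups of 5–10 women/week in self hypnosis techniques". Sub-group analyses lists "size of group < 3 women, hypnotist" among many factors, so very small groups are foreseen.
- **Analysis.** Statistical tests names "For Dichotomous outcomes: Chi squared/Relative Risks with 95% confidence intervals" and gives regression the task of examining potential confounders. Session group appears in neither.
- **Sample size.** Power calculation gives 135 per group for 80% against 64%, two-sided 0.05, 80% power, and 150 recruited to allow for 10% delivering before treatment.
- **Aim 6.** Additional specific aims sets out a comparison of the two hypnosis methods.

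**The concern.** The design is partially nested: two arms are treated in groups and the third is not. Women in one session hear the same discussion and the same answers, and may influence one another. If that makes their outcomes more alike than those of women in different groups of the same arm, each woman adds less than one independent observation. A chi-squared test and an ordinary confidence interval for a relative risk do not allow for this, and listing group size as a subgroup factor does not correct the standard error of the main comparison.

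At stake are the width of the intervals and the false-positive rate. Aim 6 is the most exposed comparison because both of its arms are grouped. Comparisons with control are less exposed because only one arm is.

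**Working it through.** **1. The plan's own figure.** Inputs from Power calculation: p1 = 0.80, p2 = 0.64, difference 0.16, mean 0.72, two-sided alpha 0.05, power 80%.

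n = [1.960 × √(2 × 0.72 × 0.28) + 0.842 × √(0.80 × 0.20 + 0.64 × 0.36)]² / 0.16² = (1.2445 + 0.5259)² / 0.0256 = 122.4, which rounds up to 123.

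Continuity-corrected: (122.4 / 4) × [1 + √(1 + 4 / (122.4 × 0.16))]² = 134.6, which rounds up to 135. This matches the stated figure exactly, and 135 / 0.90 = 150 matches the recruitment target. The calculation is for independent women and contains no allowance for session groups.

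**2. Assumed inputs.** The article gives no ICC; 0.01 to 0.05 is assumed. It gives no mean group size m; 3 to 10 is assumed, from the small groups that Sub-group analyses foresees up to the ceiling of ten.

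**3. Formulas.**
- Design effect in a grouped arm: DE = 1 + (m − 1) × ICC.
- Ratio of true to naive standard error, with equal arms and equal variance per woman: √((1 + DE) / 2) against control, √DE for Group 1 against Group 2.
- True two-sided error of a nominal 5% test: 2 × [1 − Φ(1.96 / ratio)].

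**4. Results.**

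| m | ICC | DE | SE ratio v control | True error v control | SE ratio, Group 1 v 2 | True error, Group 1 v 2 |
|---|---|---|---|---|---|---|
| any | 0 | 1.00 | 1.000 | 5.0% | 1.000 | 5.0% |
| 3 | 0.01 | 1.02 | 1.005 | 5.1% | 1.010 | 5.2% |
| 3 | 0.05 | 1.10 | 1.025 | 5.6% | 1.049 | 6.2% |
| 10 | 0.01 | 1.09 | 1.022 | 5.5% | 1.044 | 6.0% |
| 10 | 0.05 | 1.45 | 1.107 | 7.7% | 1.204 | 10.4% |

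Example, last row: DE = 1 + 9 × 0.05 = 1.45. Against control, √(2.45 / 2) = 1.107, and 1.96 / 1.107 = 1.77 gives 7.7%. For Group 1 against Group 2, √1.45 = 1.204, and 1.96 / 1.204 = 1.63 gives 10.4%. The naive interval for Group 1 against Group 2 is then 1 − 1 / 1.204 = 17% too narrow; against control, 1 − 1 / 1.107 = 10%.

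**5. Power against control at 135 per group** (80% v 64%, no continuity correction, analysis allowing for the groups): 83.7% at ICC 0, 83.3% at m = 3 and ICC 0.01, and 75.3% at m = 10 and ICC 0.05. The number needed by the plan's own continuity-corrected method rises from 135 to 136 and 164 in those last two cases.

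**The case against.** **The article condenses a fuller plan.** Regression and relative risks with intervals can carry cluster-robust errors, and such detail is commonly left to an analysis plan. That is fair for those two items. But the article also names chi-squared, and the sample size is an independence calculation. This is a stated method that does not fit the stated delivery, so the point stands.

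**The correlation may be small.** Suggestions are scripted and put on CD so that the intervention is standardised. Group 2 sessions are largely CD playback, much of the exposure is daily listening at home, missed sessions may be replaced by posted CDs, and about 10% of women are expected to deliver before treatment. All of this stands and limits the size.

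**Groups may be small.** The range of 5 to 10 describes the pre-trial clinic. At m = 3 the inflation is slight. The figures of 10.4% and 17% need every group full and the highest assumed ICC. This also stands.

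**The error figures against control need a condition.** They apply where session effects vary between groups but average to zero. If sessions have no effect of any kind, they create no such correlation.

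Several stronger readings are tempting but not supported:
- A reader might infer that the subgroup list shows the authors expect correlation within groups. It shows only that they will explore whether effects differ by group size and hypnotist.
- A reader might add shared calendar weeks as a cause. Controls are recruited and deliver over the same period, so time effects common to all arms do not act in this way.
- A reader might add the shared leader. A leader common to many groups does not create correlation specific to one session.

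**Conclusion.** The concern holds in conditional form. The article fixes an analysis and a sample size that assume independence in a design where two of three arms are treated in groups, so the standard errors are likely too small if outcomes correlate positively within session groups. A reader might infer that they are certainly too small. The documents do not support that: they give no ICC and no trial group size, and at an ICC of zero the named methods are correct.

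Under the assumed ranges the effect on comparisons with control is modest, with standard errors understated by at most about 10%. It can be material for aim 6. Power suffers less than it might, because the continuity correction left 83.7% uncorrected power at 135 per group. The change is worth making before analysis, but the point does not call the design or the recruitment target into question.

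**What to change.** - **Record** the session group each woman in Groups 1 and 2 is booked into at allocation. The article says that staff give and co-ordinate appointments, but nowhere that a group identifier is stored, so this should be confirmed or added.
- **Analyse** with that group as the cluster in Groups 1 and 2 and each control woman as her own cluster. Use either a mixed model with a random session-group effect in the hypnosis arms only, or log-binomial or Poisson regression for the relative risk with small-sample-corrected cluster-robust errors. The correction matters because 135 women in groups of ten make only about 14 groups per arm.
- **Keep** women who miss sessions, receive posted CDs or deliver early in the group they were booked into, so that intention to treat is preserved.
- **State** the assumed ICC and report the observed one.

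The cost is slightly wider intervals and the upkeep of one identifier. Allocation, recruitment and care are untouched. If the ICC proves near zero, the results will barely move. Session group alone would not capture correlation by leader if several hypnotists took part.

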### Group 1: Antenatal hypnosis plus hypnosis audio CD (hypnotherapist guided)

#### Session 1

Discussion about fears and anxieties. Questions about hypnosis answered, Seeding expectancy of success. Basic hypnosis taught using progressive relaxation with a self hypnosis component at the end. Session 1 cd played and women asked to practice this on a daily basis until the next session.

#### Session 2

After a hypnosis induction, suggestions are given for confidence, coping and strength during contractions. Women are asked to focus on breathing for analgesia and relaxation. Suggestions for time distortion: this allows contractions to seem shorter and rest periods between contractions longer than they really are. Standardised suggestions given for a labour rehearsal involving recurrent fractionation and staircase imagery[21]. Session 2 section of cd played and women asked to practice this on a daily basis until the next session.

#### Session 3

Pain control techniques – Amnesia suggestion for unhelpful comments and utilisation of helpful suggestions. Dissociation and lower body anaesthesia elicited using the lignocaine spa imagery21 Suggestions for uterine contraction after delivery and relaxation to facilitate breastfeeding. Session 3 audio cd played and women asked to practice hypnosis while listening to the whole cd on a daily basis until the birth. Women told that they can listen to the labour audio cd during labour if they wish.

### Group 2: Antenatal hypnosis audio CD (nurse guided)

#### Session 1

Structured information given regarding getting the most from the cds. An explanation is given regarding the structure of the sessions and how to obtain most benefit when listening to the cd. It is suggested not to try to pay conscious attention and to go along with any instructions given will provide optimum benefit. Questions answered and Session 1 audio cd played. Participants are asked to listen to the cd on at least a daily basis until the next session.

#### Session 2

Questions answered. Session 2 audio cd played. Participants are asked to listen to the cd on at least a daily basis until the next session.

#### Session 3

Questions answered. Session 3 audio cd played. Participants are asked to listen to the cd on at least a daily basis until the next session.

### Group 3: No intervention control

Women allocated to usual care will not be asked to attend any further sessions at the hospital other than those required for their usual antenatal care. The next involvement of these mothers will be in responding to a maternal questionnaire in the early postnatal period.

### Compliance with treatment schedules

Those women allocated to attend either of the two intervention groups are asked to listen to each session audio cd on a daily basis between the weekly sessions. Those participants who are unable to attend one or more sessions in person will be contacted by telephone to confirm all is well. We will ask the participant if we could post them the audio cd(s) of the missed session(s) for them to listen to prior to their next hospital visit. Trial participants will be able to withdraw at any stage of the trial. All randomised participants and their babies will receive follow-up in the post partum period in an identical manner regardless of the treatment actually received.

### Care during labour and the postnatal stay

This will be managed by the trial participant's attending midwife, obstetrician and neonatal team as per the usual practice of our institution.

#### Power calculation

It is proposed that sufficient women be randomised to provide reliable evidence of the effects of antenatal hypnosis regarding the primary outcome measure of this study: the incidence of not using pharmacological pain relief during labour. An audit of 100 consecutive mothers birthing at the Women's and Children's Hospital in May 2004 showed an incidence of using one or more pharmacological interventions of 80%. In order to show a clinically relevant fall of 20% in the number of women requiring pharmacological analgesia ie from 80% to 64%. Using a 2 tailed calculation (Nquery advisor computer program V.5) a study with 80% power would require each group to contain 135 women to detect this difference at the 0.05 level.

Complete collection of the primary endpoint is likely as all analgesia techniques used such as Entonox, pethidine and epidural analgesia are documented routinely in the labour ward birth register and medical record by the woman's treating midwife. We plan to recruit 150 women/group as we estimate that 10% of participants' will deliver prior to receiving their allocated treatment. The findings of our case matched control study at the Women's and Children's Hospital[47] are consistent with those of our systematic review of the literature on this topic [22]. No comparative trials have investigated the effects of hypnosis on the incidence of postnatal depression although acknowledged experts in the field report a low incidence in women taught hypnosis (<1%) [21]. The prevalence of post-natal depression in several recent studies in Australia is between 13 and 18% [63]. Our proposed study has a power of 80% at the 0.05 level of significance to show a reduction from 16% to 5.4% for this secondary outcome. For normally distributed continuous measures (eg EPDS) we would be able to detect shifts of 0.4 SD with a power of 80 % between individual arms of the study (n = 135 per group). Comparisons which exploit the two treatment groups (assuming a conservative estimate of postnatal data in 270 subjects in Groups 1 and 2) would have 80% power to detect a shift of only 0.28 SD.

**[see **Additional file 2**] **for estimated detectable differences in key endpoints with sample size of 135/group. Based on these estimates a total recruitment of 450 women will enable detection of significant differences of clinical relevance for the primary outcome and for some key secondary outcomes. We recognize that a trial of this size may be too small to detect differences in the risk of some of our secondary endpoints but the information will allow comparisons of women in other hypnosis studies in a systematic review or suggest other beneficial outcomes or adverse effects that require further controlled evaluation.

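### The step from 135 to 150 per arm treats women who deliver before treatment as lost, but intention to treat keeps them in; 80% power then holds across the plan's 5–10% range only with an uncorrected chi-squared test

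*Protocol article*

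**What the plan says.** All references are to the protocol article.

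- **Power calculation.** The target is a "clinically relevant fall of 20% in the number of women requiring pharmacological analgesia ie from 80% to 64" per cent, and "a study with 80% power would require each group to contain 135 women to detect this difference at the 0.05 level". Recruitment is then raised: "We plan to recruit 150 women/group as we estimate that 10% of" women are expected to give birth before they receive what they were allocated. The abstract puts this proportion at about 5–10%.
- **Power calculation, on the outcome.** "Complete collection of the primary endpoint is likely", because analgesia is routinely entered in the birth register and the medical record.
- **Compliance with treatment schedules.** "All randomised participants and their babies will receive follow-up in the post partum period in an identical manner regardless of the treatment actually received". Women who miss a session are telephoned and offered the missed CD by post.
- **Analyses.** Every primary and secondary outcome is analysed by intention to treat.
- **Sub-group analyses.** "Some women will not attend the sessions to which they are allocated". Women who give birth before finishing the three sessions are analysed by intention to treat, and also with session exposure as a predictor.
- **Statistical tests.** Dichotomous outcomes get a chi-squared test and relative risks with 95% confidence intervals. Whether the test carries a continuity correction is not said.

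**The concern.** Dividing by 0.9 is right when 10% of women have no outcome: 150 are randomised, 135 are analysed, and the contrast stays at 80% v 64%. Here the outcome is expected for nearly everyone, and a woman who delivers before her first session stays in her hypnosis arm without having had hypnosis. The number analysed is then 150, not 135, but the difference between arms is smaller. The extra 15 women per arm have to pay for a diluted effect, and the inflation was not calculated for that.

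At stake is whether the 80% power for the primary endpoint, given in the abstract and behind the total of 450, describes the comparison that will actually be made.

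**Working it through.** **Inputs from the protocol article:** control rate 80%; hypnosis rate 64%; two-sided 0.05; 80% power; equal arms; 135 raised to 150 per arm; 10% untreated (Power calculation) or 5–10% (abstract).

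**Assumptions (not stated in the document):** 64% is the rate among treated women; untreated women in a hypnosis arm have the control rate of 80%.

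**1. Reproduce 135.** Write d for the difference and p̄ for the mean of the two rates. The uncorrected size per arm is

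m = [1.960·√(2p̄(1−p̄)) + 0.8416·√(p₁(1−p₁) + p₂(1−p₂))]² / d²

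For 0.80 v 0.64, p̄ = 0.72 and d = 0.16, so m = (1.2445 + 0.5259)² / 0.0256 = 122.4.

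The continuity-corrected size is n = (m/4)·[1 + √(1 + 4/(m·d))]² = 134.6, so 135. The plan's figure is the continuity-corrected one; without the correction it would be 123.

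**2. Reproduce 150.** 135/(1 − 0.10) = 150 exactly, the formula for loss from the analysis.

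**3. Intention-to-treat contrast with 10% untreated.** 0.9 × 64 + 0.1 × 80 = 65.6%. The difference falls from 16 to 14.4 points.

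**4. Power at 150 per arm, 80% v 65.6%.**

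- Uncorrected: z = (0.144·√150 − 1.2334)/0.6210 = 0.854, so power is 80.3%. Exact enumeration of the uncorrected test gives 80.7%.
- Corrected: inverting the formula in step 1, m = (n·d − 1)²/(n·d²) = (21.6 − 1)²/(150 × 0.020736) = 136.4. Then z = (0.144·√136.4 − 1.2334)/0.6210 = 0.722, so power is 76.5%. Exact enumeration gives 76.7% with the Yates correction and 77.1% with Fisher's test.

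**5. Size needed for 80% power at this contrast.** Uncorrected 148.7, so 149; corrected 162.3, so 163.

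**6. Across the untreated fraction, 150 per arm:**

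| Untreated | Hypnosis-arm rate | Power, corrected | Power, uncorrected |
|---|---|---|---|
| 0% | 64.0% | 84.5% | 87.4% |
| 5% | 64.8% | 80.7% | 84.1% |
| 7.5% | 65.2% | 78.7% | 82.3% |
| 10% | 65.6% | 76.5% | 80.3% |
| 15% (assumed) | 66.4% | 71.8% | 76.0% |
| 20% (assumed) | 67.2% | 66.6% | 71.3% |

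The last two rows lie outside the plan's range. They show only what would follow if non-attendance came on top of early delivery and every such woman had the control rate.

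**The case against.** A reader might infer that the trial simply has about 76% power, not 80%. The document does not support that. The 76.5% needs both the upper end of the abstract's range and a continuity-corrected test at analysis. The plan names a chi-squared test without mentioning a correction, and a corrected formula is often used only to choose a cautious sample size. With the uncorrected test, 150 per arm delivers 80.3% even at 10% untreated. At 5% untreated, either version exceeds 80%. This part of the objection stands.

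A reader might also infer power of about 72% or 67% from the 15% and 20% rows. The document gives no such rates. It also offers the missed CDs by post, the CD is itself the Group 2 intervention, and most of the skills are said to be taught in the first session. A woman who misses a session is not necessarily untreated. This also stands, so those rows remain scenarios.

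If 64% were already meant as the intention-to-treat rate, power at 150 would be 84.5% (corrected). That is possible, but enlarging the trial for women who never receive treatment would then have no purpose.

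Last, other inputs are less certain than this. The 80% control rate comes from an audit of 100 births, so its standard error is √(0.8 × 0.2/100) = 4 points. With the same 20% relative fall, a control rate of 76% gives 72.7% power at 135 per arm and 84% gives 87.2% (corrected). That is a fair reason to call the shortfall modest. It does not make the inflation fit the analysis, and unlike the control rate this can be settled in the text.

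**Conclusion.** The reasoning behind the inflation does not match the planned analysis: it allows for loss where the plan produces dilution. The consequence is modest and conditional. At 150 per arm, power for the pairwise intention-to-treat contrast runs from 80.7% down to 76.5% over 5–10% untreated on the plan's own continuity-corrected calculation, and from 84.1% down to 80.3% with the uncorrected test. The largest shortfall within the plan's own figures is thus about 3.5 points. The 80% claim holds over the whole range only with the uncorrected test. Even then, 0.3 points remain at 10%, which is no margin for the further non-attendance that the plan expects.

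This rests on 64% being the rate in treated women, on untreated women having the control rate, and on a comparison of one hypnosis arm with control.

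**What to change.** Keep 450 women and change the text in four places:

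1. In the power calculation, say that the extra 15 women per arm offset dilution by women who deliver untreated, not loss of outcome data.
2. Restate power at 150 per arm for the intention-to-treat contrast over 5–10% untreated (80% v 64.8% to 65.6%), with the two assumptions written out.
3. Add the 15% and 20% rows if wanted, labelled as assumed non-attendance scenarios.
4. Under Statistical tests, name the chi-squared test without continuity correction as the primary test, before any unblinded look at the data.

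The cost is a few sentences. No more women are needed with that test, and no change to the timing of randomisation is called for. If the team prefers a continuity-corrected test, it should either report 76.5% at 10% untreated or recruit 163 per arm.

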#### Further follow up

Postnatal questionnaires will be sent to each participant at 6 weeks and 6 months after the birth where the EPDS[61] and Spielberger anxiety scales[60] will be repeated. Women will be asked whether they are still breast feeding and invited to make comments of any problems or difficulties with the intervention. Two weeks after postage of postnatal questionnaires there will be follow-up by telephone call at home for non-responders.

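### Baseline EPDS and anxiety scores are collected, but adjustment for them depends on seeing a chance imbalance; it should be pre-specified for the postnatal depression and anxiety analyses

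*Protocol article*

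**What the plan says.** All references are to the Protocol article.

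- **Baseline.** Under Interventions and comparisons, participants complete the Spielberger "anxiety[60] and Edinburgh post-natal depression scales[61" at entry. The section on psychological testing confirms that both scales are given before the allocated treatment.
- **Follow-up.** "Postnatal questionnaires will be sent to each participant at 6 weeks and 6 months after the birth where the EPDS[61" and the anxiety scale are repeated.
- **Power for depression.** The trial is said to have 80% power, testing at 0.05, "to show a reduction from 16% to 5.4% for this secondary outcome". The next two sentences of that section also power EPDS as a continuous measure: 0.4 SD between single arms, and 0.28 SD when the two hypnosis groups are used together.
- **Tests.** "For Dichotomous outcomes: Chi squared/Relative Risks with 95% confidence intervals". The same section adds a general statement that regression will examine potential confounders. It does not name baseline EPDS or baseline anxiety.
- **Adjustment rule.** The Analyses section takes baseline differences into account in later analyses if chance differences between groups are found.
- **Stratification.** Randomisation is stratified for parity.
- **Status.** The Discussion lists the incidence of postnatal depression as a key endpoint and as one of the trial's novel features.

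**The concern.** A baseline score is worth including because it predicts the follow-up score, and that holds whether or not the arms happen to differ at baseline. A rule triggered by observed imbalance gets this the wrong way round. When the arms look balanced, the covariate is left out and its precision is lost. When they do not, covariates are chosen after the data have been inspected, and the article does not say what counts as a difference. At stake is the sensitivity of the depression and anxiety comparisons, and the credibility of whichever model is finally reported.

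**Working it through.** **Inputs.** Rates of 16% and 5.4%, power 80% and level 0.05 come from the Power calculation section. The group size of 135 comes from the pointer to Additional file 2, "for estimated detectable differences in key endpoints with sample size of 135/group". Two-sidedness is stated for the primary outcome ("Using a 2 tailed calculation (Nquery advisor computer program V.5") and assumed here. The correlation r between baseline and postnatal EPDS is not in the document; I assume 0.3 to 0.7.

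**1. The plan's own figure.** Two-proportion test, pooled variance, no covariate, no continuity correction:
- mean rate = (0.16 + 0.054)/2 = 0.107; difference = 0.106
- SE under the null = √(2 × 0.107 × 0.893/135) = 0.0376
- SE under the alternative = √((0.16 × 0.84 + 0.054 × 0.946)/135) = 0.0371
- z = (0.106 − 1.96 × 0.0376)/0.0371 = 0.87, so power = 80.8%

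With a continuity correction, 5.4% is the detectable rate at 150 per group (4.9% at 135). By either route the figure contains no baseline term.

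**2. Continuous EPDS, unadjusted.** Detectable shift = (1.960 + 0.842) × √(2/135) = 2.802 × 0.1217 = 0.341 SD. The stated 0.4 SD has 90.8% power at 135 per group. For 270 versus 135 the 80% figure is 2.802 × √(1/270 + 1/135) = 0.295 SD; the stated 0.28 SD corresponds to 300 versus 150 (2.802 × 0.100). These figures are loose, but they show that a continuous comparison was foreseen, again with no allowance for baseline.

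**3. Continuous EPDS, baseline-adjusted.** Multiply 0.341 by √(1 − r²). The equivalent unadjusted group size is 135/(1 − r²).

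| assumed r | detectable shift (SD) | equivalent n per group |
|---|---|---|
| 0.3 | 0.325 | 148 |
| 0.4 | 0.313 | 161 |
| 0.5 | 0.295 | 180 |
| 0.6 | 0.273 | 211 |
| 0.7 | 0.244 | 265 |

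**4. Incidence, baseline-adjusted.** Simulation, 1,500 runs per setting, of a normal score cut so that 16% of controls exceed the threshold, with a uniform shift giving 5.4% in the treated arm and 135 per group. Power was about 82% by chi-squared. By logistic regression with the baseline score it was 86%, 87%, 88% and 91% for r = 0.4, 0.5, 0.6 and 0.7. At a true fall to 9% the corresponding figures were about 42% and 45–54%.

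**5. What the trigger leaves in.** As an illustration, suppose a difference counts as found only when a 5% test is significant (the article gives no definition). A baseline difference of up to 1.96 × 0.1217 = 0.239 SD would then go uncorrected. It would move the unadjusted follow-up difference by r × 0.239, which is 0.07 to 0.17 SD for r = 0.3 to 0.7, against a detectable shift of 0.34 SD.

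**The case against.** The strongest reply is that an unadjusted power calculation is ordinary and does not fix the analysis model. The article allows baseline differences to be taken into account, promises regression, and names no test for continuous EPDS, so nothing rules out ANCOVA. Covariate lists for secondary outcomes are commonly left to an analysis plan, and the article concedes that the trial may be too small for some secondary endpoints. The analyst is also blinded to allocation, which limits selective modelling.

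Much of this stands, and it disposes of several stronger readings that a reader might infer:
- *That only a two-thirds fall in depression is detectable.* The 66% reduction (10.6/16) applies to the arm-versus-arm incidence comparison only. The continuous comparison is powered in the next sentences.
- *That baseline EPDS is excluded from the analysis.* Adjustment is conditional, not excluded.
- *That 16% and 5.4% are rates of EPDS above 12.* This is plausible but not stated. The threshold appears as a level for clinical action, not as the definition behind those rates.
- *That the missing baseline explains the large detectable effect.* On a normal scale, 16% to 5.4% is a shift of 1.607 − 0.994 = 0.61 SD. The step from 0.61 to 0.34 SD comes from dichotomising; the baseline score accounts only for the further step to 0.325–0.244 SD.
- *That mean score must replace incidence as the main depression result.* The two answer different questions, and choosing incidence for its clinical meaning is legitimate.

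What the reply does not meet is that the article is not silent on adjustment. It states a rule, and the rule depends on the data.

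**Conclusion.** The point holds in this limited form: the plan collects a prognostic baseline score for depression and for anxiety, but makes its use depend on observed imbalance. For the EPDS score, pre-specified adjustment lowers the detectable shift at 135 per group from 0.341 SD to between 0.325 and 0.244 SD. For incidence the gain is modest, from about 82% to 86–91% power at 16% versus 5.4%. At the low end of the assumed correlation the precision gain is small; the benefit of settling the model in advance remains.

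The sizes rest on the assumed correlation (0.3 to 0.7 for the score, 0.4 to 0.7 for incidence), on a normal score with a uniform shift (EPDS may be skewed), and on 135 women per group with postnatal data. Non-response would lower power: at 120 per group the unadjusted incidence comparison has about 76%.

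**What to change.** Replace the imbalance-triggered rule with adjustment fixed in advance:

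- **EPDS and anxiety scores:** ANCOVA at each time point, or one repeated-measures model for 6 weeks and 6 months, with the baseline value of the same score and parity (the randomisation stratifier) as covariates.
- **Depression incidence:** a regression including arm, baseline EPDS and parity, reported as an adjusted relative risk to match the effect measure already chosen, with the unadjusted result beside it. Keep the covariate list short: 135 × 0.16 + 135 × 0.054 gives only about 29 cases in a two-arm comparison. State the definition of a case.
- **Hierarchy:** incidence may stay the key depression endpoint, with the adjusted score analysis reported alongside.

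No new data are needed. Recruitment began in December 2005 and main secondary outcomes are due for interim review at 150 and 300 participants, so the change should be a dated entry in the protocol or analysis plan, made without knowledge of outcome results by arm.
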